### Neuroendocrine testing

The difference between plasma cortisol concentrations obtained pre- and post-dexamethasone will be used to calculate cortisol suppression (post-pre). Cortisol suppression will then be compared across groups by performing a linear regression of the change in cortisol level from Day 2 to Day 1 (8 am levels), while controlling for Day 1 8 am level as a covariate. Presence of dexamethasone in the Day 2 sample will confirm that the participant has taken the drug. Because individual differences in dexamethasone bioavailability can alter post-dexamethasone cortisol suppression, plasma dexamethasone concentrations will be used as a covariate in statistical analyses. The difference between salivary cortisol peak and trough will be calculated to achieve an estimate of range, which can be compared across groups using a Wilcoxon rank sum test.

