## Background

Posttraumatic stress disorder (PTSD) is a chronic and prevalent anxiety disorder that follows exposure to an overwhelming traumatic event [1]. The majority of patients with PTSD also meet criteria for other psychiatric disorders and experience significant functional impairment [2]. Many also attempt suicide [3]. Despite its impact on society, there is only partial understanding of the etiology or pathophysiology of this disorder. Effective pharmacotherapy options remain limited, with only sertraline and paroxetine approved by the US Food and Drug Administration (FDA) for PTSD. Response rates to these selective serotonin reuptake inhibitors (SSRIs) rarely exceed 60%, and even fewer patients (20 to 30%) achieve clinical remission [4]. The Institute of Medicine’s review of treatments for PTSD concluded that there is insufficient evidence to support the use of any medication for PTSD [5]. Thus, there is a clear need to develop novel and improved therapeutics for PTSD.

A growing body of literature suggests that stress-related disorders such as PTSD are associated with chronically increased activity of central nervous system circuits that utilize the 41 amino acid peptide neurotransmitter corticotropin releasing hormone (CRH, also known as corticotropin releasing factor, CRF). CRH mediates the neuroendocrine, immune, autonomic, and behavioral responses to stress [6]. CRH levels are increased by stress, resulting in activation of the hypothalamic-pituitary-adrenal (HPA) axis and increased release of cortisol and other adrenal steroids. In addition, extrahypothalamic neurons containing CRH are located throughout the brain, including the prefrontal and cingulate cortices, central nucleus of the amygdala, bed nucleus of the stria terminalis, nucleus accumbens, periaqueductal gray, and brain stem nuclei such as the major norepinephrine-containing nucleus, the locus ceruleus, and the serotonin nuclei in the dorsal and median raphe [7]. PTSD has been associated with abnormalities in HPA axis hormones, both basal and after low-dose dexamethasone dosing [8].

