##### 4. Neuroendocrine evaluation

Salivary samples are a validated means of non-invasively estimating circadian cortisol rhythms and of monitoring the dexamethasone suppression response for use as a marker of PTSD. At Visit 1, subjects are given pre-labeled Salivette collection tubes (Sarstedt, Rommesldorf, Germany) and instructed in the sample collection process. On the morning of Visit 2, one day prior to randomization, participants collect three salivary samples: (1) immediately upon awakening (and prior to eating); (2) 30 minutes after awakening, and (3) 60 minutes after awakening. Participants come to the clinic for Visit 2 at 8 am for the venipuncture collection of plasma cortisol and ACTH levels. Upon completion of Visit 2, participants are given two more Salivettes and one pill of dexamethasone 0.5 mg. On the night of Visit 2, participants collect the fourth salivary sample at 11 pm, followed immediately by ingestion of the dexamethasone. On the morning of Visit 3, subjects collect the fifth salivary sample upon awakening and return to the clinic at 8 am for the post-dexamethasone venipuncture for plasma cortisol and ACTH levels. This two-day procedure is repeated at Visits 7 and 8 in order to assess change in the neuroendocrine measures after five weeks on study medication. Due to confounding of HPA measures stemming from altered circadian rhythms, night-shift workers do not complete this component of the study.

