### Psychophysiological testing

For the fear-potentiated startle paradigm, the mean startle magnitude for each CS type in each block will be used to calculate percent change scores with the following formula using noise alone (NA) trials as the reference:

$$\begin{array}{ll} \mathrm{Percent}\mathrm{potentiation} & =100*\left(\mathrm{CS}\;\mathrm{startle}\;\mathrm{magnitude}\right)\\ & –\;\left(\mathrm{NA}\;\mathrm{startle}\;\mathrm{magnitude}\right)\\ & /\left(\mathrm{NA}\;\mathrm{startle}\;\mathrm{magnitude}\right) \end{array}$$

Discrimination between danger and safety signals will be calculated as the difference in potentiation between CS + and CS − trials. Fear inhibition will be assessed as the difference between the reinforced trials during conditioning (AX+) and the transfer trials containing elements of CS + and CS − (which are AB trials). Finally, fear extinction will be measured as the decrease in response to the CS + during the extinction session. Given the assumption of significant individual variation in the psychophysiological measures, we will perform mixed effects linear models comparing treatment group for each fear-potentiated startle measure (conditioning, discrimination, transfer of safety, and extinction) with Block, Time (baseline versus six weeks) as the within-subjects factor and Group (GSK561679 versus placebo) as the between-subjects factor and including a random intercept. The effect of interest will be the group*time interaction, indicating a significant difference between groups in change in startle over time. Skin conductance response will be analyzed in a parallel manner. Contingency awareness will be analyzed by comparing US-expectancy ratings for each CS trial type in a parallel manner.

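### The cortisol-suppression regression names no visits, omits the pre-randomisation test and adjusts for an 8 am cortisol the drug may shift, so its treatment coefficient matches no clear effect

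*Protocol article*

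**What the plan says.** Section 4, Neuroendocrine evaluation, describes a two-day test: 8 am plasma cortisol, dexamethasone that night, and 8 am plasma cortisol again the next morning. It is done first at Visits 2 and 3, before treatment starts. "This two-day procedure is repeated at Visits 7 and 8 in order to assess change in the neuroendocrine measures" once patients have had five weeks of drug or placebo.

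The Neuroendocrine testing section then defines suppression as post minus pre and compares groups by a "linear regression of the change in cortisol level from Day 2 to Day 1 (8 am levels". The first day's morning cortisol enters that regression as an adjustment term. It adds that "plasma dexamethasone concentrations will be used as a covariate in statistical analyses". Days 1 and 2 are the two days of one test. The section does not say whether that test is the one at Visits 2-3 or the one at Visits 7-8, and the day numbers in Table 1 (-1, 0, 35, 36) do not settle it. The model has no baseline-test covariate, no time term and no group-by-time term.

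The Psychophysiological testing section handles the same two-occasion design differently: "The effect of interest will be the group*time interaction".

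**The concern.** Visits 2-3 precede treatment, so a comparison there can show no drug effect. A treatment comparison under the stated model therefore has to use Visits 7-8, where the Day 1 cortisol covariate is measured on drug. The Background section links CRH to "activation of the hypothalamic-pituitary-adrenal (HPA) axis and increased release of cortisol", and the study drug blocks a CRH receptor. Morning cortisol is thus something the drug might plausibly change, and comparing arms at equal on-drug morning cortisol is not a comparison that randomisation protects.

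The model also leaves out the pre-randomisation test, although the test is repeated expressly "in order to assess change in the neuroendocrine measures after five weeks on study medication". HPA-axis hormones are among the secondary aims, and the Discussion expects dexamethasone suppression to be informative even if the drug fails on symptoms. At stake is a suppression result that cannot be read: an apparent effect, or an apparent absence of one, that depends on what the drug does to morning cortisol.

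**Working it through.** The article gives no figure for this analysis, so there is none to reproduce.

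**1. The coefficient.** Let Y1 and Y2 be pre- and post-dexamethasone 8 am cortisol at Visits 7-8, d1 and d2 the drug's shifts in them, and b the within-arm slope of Y2 on Y1. Regressing Y2 - Y1 on group and Y1 gives the same group coefficient as regressing Y2 on group and Y1:

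- planned coefficient = d2 - b*d1
- effect on suppression = d2 - d1
- effect on post-dexamethasone cortisol = d2

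If d1 = 0, all three agree. If not, they generally differ:

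- No effect on post-dexamethasone cortisol (d2 = 0): coefficient = -b*d1.
- No effect on suppression (d1 = d2 = d): coefficient = (1 - b)*d.
- Masking: with b = 0.5, d1 = -0.5 and d2 = -0.25, the coefficient is -0.25 + 0.25 = 0, while suppression changes by +0.25 and post-dexamethasone cortisol by -0.25.

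**2. Size.** From the document: 50 completers per group (Statistical power/sample size). Assumed: both SDs = 1, so b equals the within-test correlation r; r = 0.3 or 0.5; shift d1 = -0.3 or -0.5 SD; two-sided 0.05. The dexamethasone covariate is not modelled.

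SE = sqrt[(1 - r²)(2/50 + d1²/100)]. For r = 0.5 and d1 = -0.5: sqrt(0.75 × 0.0425) = 0.179. A coefficient of 0.25 is then 1.40 SEs, which is rejected in about 28% of trials.

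| d1 | r | SE | d2 = 0: coefficient, rejection | d2 = d1: coefficient, rejection |
|---|---|---|---|---|
| -0.3 | 0.3 | 0.193 | +0.09, 8% | -0.21, 19% |
| -0.5 | 0.3 | 0.197 | +0.15, 12% | -0.35, 42% |
| -0.3 | 0.5 | 0.175 | +0.15, 14% | -0.15, 14% |
| -0.5 | 0.5 | 0.179 | +0.25, 28% | -0.25, 28% |

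Simulation agrees: about 7-30% under the first null and 13-43% under the second. The apparent effect has opposite signs under the two nulls. If Day 2 SD is half of Day 1 SD and both samples shift equally, rejection is about 71-75% for a 0.3 SD shift and 98-99% for 0.5 SD. With no shift in either sample it is about 4-6%.

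**3. With pre-randomisation covariates.** Adjusting for Visit 2-3 values instead of on-drug Day 1 cortisol gives about 3-6% rejection for each estimand under its own null.

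**4. Precision.** Equal SDs, r = 0.3, no shift, suppression as outcome:

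- no covariates: sqrt(2 × 0.7 × 2/50) = 0.237
- planned model: sqrt(0.91 × 2/50) = 0.191
- Visit 2-3 covariates in place of Day 1: 0.227, 0.207 or 0.171 at retest correlation 0.3, 0.5 or 0.7

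Baseline adjustment therefore always improves on the same outcome without it, but beats the planned SE only at retest correlation 0.7. With Day 2 SD halved, the SE rises from 0.096 to 0.187, 0.170 or 0.140.

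**The case against.** The strongest reply is that this is a condensed article. It names no visits, so the on-drug reading is an inference, and how the two occasions enter the model could be settled in a fuller plan. That stands as a limit: a reader might infer that the trial discards its baseline test, and the text does not go so far. It does not dispose of the point, because the outcome and covariates are stated, and a treatment comparison with them can come only from Visits 7-8.

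Four stronger readings are tempting and are not supported:

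- **The model finds a drug effect where none exists.** If post-dexamethasone cortisol is unchanged and morning cortisol falls, post minus pre has truly changed. A baseline-adjusted analysis of suppression then rejects in 26-93% of trials (equal SDs), correctly. The 7-30% is a false-positive rate only for the effect on post-dexamethasone cortisol; the 13-43% is the rate for suppression. The two nulls must be kept apart.
- **The model loses precision.** This is true against adding baseline to the same model, but not in general against replacing the on-drug covariate.
- **The dexamethasone level carries a drug effect.** Nothing in the document says the study drug alters it, and the stated reason for adjusting, individual bioavailability, is sensible. It is simply also a post-randomisation value.
- **The salivary rank-sum comparison is wrong.** It is a valid comparison of randomised arms. Baseline adjustment there is optional.

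**Conclusion.** The point holds in a limited form. Read as a treatment comparison, the stated model conditions on a post-randomisation cortisol and does not use the repeat-test design. If the drug moves morning cortisol, its coefficient is in general neither the effect on suppression nor the effect on post-dexamethasone cortisol. Rejection is then about 7-30% or 13-43%, according to which effect is truly absent.

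These rates rest on assumed shifts, correlations and equal SDs. The document makes a cortisol shift plausible but gives no size, and without one type I error is nominal. Fifty per arm is optimistic, since night-shift workers skip the test; fewer patients would lower the rejection rates but not the distortion in the coefficient.

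The importance is moderate. HPA hormones are a secondary aim in the Aims section, but Table 1 lists the neuroendocrine measures as exploratory. A reader might infer a threat to the trial's main conclusion; the CAPS analysis does not use these data.

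**What to change.** - State that the treatment comparison uses Visits 7-8, and define Days 1 and 2 by visit.
- Choose one estimand: Visit 7-8 suppression, or Visit 8 post-dexamethasone cortisol.
- Compare it between arms adjusting for the Visit 2-3 values of the same test, or fit a group-by-time model as for startle.
- Label any analysis adjusted for on-drug 8 am cortisol or on-drug dexamethasone level as explanatory.

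No new data are needed. The costs are a rule for patients without a pre-randomisation test and, if suppression is the estimand, possibly a larger SE than the planned model would report.

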### Cognitive function

Using the computer program provided with the MATRICS battery, we will develop a composite score for use in the exploratory analyses of the role of neuropsychological variables in treatment response. This score is a standard (that is ‘t’) score, so that changes from baseline are easily interpretable in terms of their effect sizes. We will also perform additional exploratory analyses of those tests in the battery specifically shown to be sensitive to PTSD in prior studies (Hopkins Verbal Learning Test and letter-number span).

### Moderator analyses

We have *a priori* specified factors that we expect may moderate the treatment effect in PTSD subjects [47]. These include, age, type and age of trauma exposure, and past treatment history. While the study is not specifically powered to detect these effects, we will analyze treatment by subgroup interaction effects in these exploratory analyses in order to provide important information for the design of future, more definitive studies. We will determine significant moderators by specifically testing the treatment by variable interaction added to the analysis of the primary outcome. Given the limited sample size, each possible moderator will be analyzed separately.

#### Statistical power/sample size

As this is the first trial of a CRHR1 antagonist in PTSD, we do not have any pilot data from which to estimate an effect size. Our sample size calculation of 154 subjects is based on an effect size of seven CAPS points, consistent with the observed difference in the study by Davidson and colleagues of the efficacy of sertraline for PTSD [48]. We used that study’s effect size and pooled between-subjects standard deviation, and expected early termination rates, to construct our power calculation on the specific test of the treatment group-by-time (two timepoints, pre and post) interaction effect for a standard repeated measures analysis of variance [49]. We used an alpha of 0.05 for all main effects and the interaction, and calculated that a sample size of 50 completers per group allows us to detect an interaction effect of this size with a power of 0.91. With the expected dropout rate of 35%, this requires recruitment of 77 subjects per group to meet the anticipated endpoint sample size, for a total randomized sample of 154 subjects.

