### Major endpoints

The primary outcome is mean change on the CAPS past-week score between the two treatment arms. Secondary outcomes include response and remission on the CAPS past-week score. Response is defined as ≥ 50% reduction from the baseline CAPS total score at the final on-drug study visit (V9 for completers). Remission is defined as a CAPS score ≤ 20 at the final on-drug visit.

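### The power of 0.91 for a 7-point CAPS difference holds only if the SD of CAPS change is about 10.5 or less, and the inputs needed to check this are not reported

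*Protocol article*

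**What the plan says.** All the sample-size reasoning is in the protocol article under Statistical power/sample size.

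- The calculation is "based on an effect size of seven CAPS points", taken from a cited sertraline trial in PTSD.
- From that study the authors took the "effect size and pooled between-subjects standard deviation", together with expected early termination rates. No value is printed for the SD.
- The test powered is the "treatment group-by-time (two timepoints, pre and post) interaction effect for a standard repeated measures analysis of variance".
- On the error rate: "We used an alpha of 0.05 for all main effects and the interaction".
- The result: "a sample size of 50 completers per group allows us to detect an interaction effect of this size with a power of 0.91".
- With 35% dropout this becomes 77 per group, 154 in total.

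Under Data analyses, Primary analysis, the planned method is different: a likelihood-based mixed effects model under intention to treat, assuming data missing at random. Table 1 schedules the CAPS at baseline and at weeks 1, 2, 4 and 6 of treatment. Under Site effects, the plan tests for site differences and, if they are significant, replaces the proposed analyses with stratified ones.

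**The concern.** The SD that the article names is not the one that sets the power of this test. A between-subjects SD describes how patients differ at one time. The interaction test compares changes, and the SD of change also depends on how strongly the pre and post scores correlate. The section mentions no correlation. The article reports effect, alpha, completers, dropout and power, but not the two inputs that decide whether these figures fit together.

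This figure is the only justification given for the trial's size. If the trial finds no difference, readers will weigh that result as coming from a study with 91% power for seven points. Whether that is fair depends on an SD of change that they cannot see. The figure also belongs to a completer analysis at two timepoints, which is not the analysis the trial plans to run.

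**Working it through.** **Inputs from the document.** Difference δ = 7 CAPS points; n = 50 completers per arm, allocated 1:1; α = 0.05; power 0.91; dropout 35%. Sidedness is not stated. The ANOVA F-test with one degree of freedom is equivalent to a two-sided t-test, so two-sided is used here.

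**1. Dropout step.** 50 / (1 − 0.35) = 76.9, rounded up to 77 per arm and 154 in total. The plan's figure reproduces.

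**2. The stated power.** It cannot be reproduced forward, because neither the SD nor the correlation is given. Solving backward:

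- Normal approximation: SD of change = δ·√(n/2) / (z₀.₉₇₅ + z₀.₉₁) = 7 × 5 / (1.960 + 1.341) = 10.6.
- Noncentral t with 98 degrees of freedom: 10.5.
- Standardized effect: 7 / 10.5 = 0.67.
- Letting the power vary from 0.89 to 0.93 moves the SD only from 10.9 to 10.1. A one-sided test would allow 11.6.
- If all 77 per arm contributed fully, the limit for 0.91 would be 13.1.

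**3. What a between-subjects SD would need.** With equal SDs before and after, SD of change = SD·√(2(1 − ρ)), so ρ = 1 − 10.5² / (2·SD²). The document gives no SD, so these values are assumed:

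| Between-subjects SD (assumed) | Pre-post correlation needed for 0.91 |
|---|---|
| 12 | 0.62 |
| 15 | 0.76 |
| 20 | 0.86 |
| 25 | 0.91 |

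For example, at SD 20: 1 − 110.25/800 = 0.86.

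**4. Power at other SDs of change** (noncentral t, two-sided, δ = 7). The 77-per-arm column treats every randomized patient as fully informative, so it is an upper bound on what partial data can add to this change-score comparison.

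| SD of change (assumed) | 50 per arm | 77 per arm |
|---|---|---|
| 10.5 | 0.91 | 0.98 |
| 12 | 0.82 | 0.95 |
| 15 | 0.64 | 0.82 |
| 20 | 0.41 | 0.58 |

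**5. Powered test against planned test.** The calculation covers completers, two timepoints and a repeated measures ANOVA. The planned analysis covers all randomized patients, repeated visits and a mixed model under missing at random. The second can use partial data from patients who leave early, so 50 per arm understates its information. But the article links no power figure to it.

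**The case against.** The strongest reply is that no error has been shown. A figure that cannot be recomputed cannot be called wrong. The section names the study that supplied the SD and cites a method for the calculation. A repeated measures calculation may properly take a between-subjects SD plus a correlation, and an SD of 15 with a correlation of 0.76 would give 0.91. A journal article may also leave such inputs to the full protocol. This stands, and it limits the point: 0.91 is conditional and unverifiable, not refuted.

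A reader might go further and infer from the Background that true power is far lower. That section says "Response rates to these selective serotonin reuptake inhibitors (SSRIs) rarely exceed 60%, and even fewer patients (20 to 30%) achieve clinical remission", and Major endpoints says "Remission is defined as a CAPS score ≤ 20 at the final on-drug visit". Assume those definitions, normal scores and one common baseline B. The implied SD is then (B/2 − 20) / (z₀.₆₀ − z of the remission rate). At B = 70 this is 15/1.095 to 15/0.778, or about 14 to 19. The documents do not support the inference, for three reasons:

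- Nothing says the cited response and remission rates use this trial's definitions.
- No mean baseline is given. At B = 60 the same formula gives 10/1.095 to 10/0.778, or about 9 to 13, which includes 10.5.
- A common baseline makes the endpoint SD equal to the SD of change. Allowing a baseline SD of 12 around a mean of 65, with 20% remission, the implied SD of change is 13.9, 11.9 or 9.3 at correlations of 0.3, 0.5 or 0.7.

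A reader might also take the group-by-time interaction expected under Response rates as a sign that the primary test is a joint test over all visits, with correspondingly lower power. That expectation concerns the secondary binary outcome. Nothing makes such a joint test primary, and Major endpoints defines the primary outcome as mean change.

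**Conclusion.** The point holds in a conditional form. The stated power of 0.91 requires an SD of CAPS change of about 10.5 or less with 50 per arm, or 13.1 or less if all 77 per arm were fully informative. The article names a source for a between-subjects SD but reports neither its value nor the correlation, so the requirement cannot be checked. Power is sensitive to this input: moving from 10.5 to 15 takes it from 0.91 to 0.64 with 50 per arm.

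The document contains no SD, so it does not show that 0.91 is wrong or that actual power is low. The values at 12, 15 and 20 are assumptions that show the range. They rest on a two-sided 0.05 test, a 7-point difference and normal change scores. Separately, and without any assumption about the SD, the powered test is not the planned primary analysis.

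**What to change.** 1. **State the inputs.** Under Statistical power/sample size, give the between-subjects SD, the pre-post correlation and the resulting SD of change. For example: *With 50 completers per arm and a 7-point difference, power is 0.91 if the SD of CAPS change is 10.5, 0.82 at 12, 0.64 at 15 and 0.41 at 20. Our calculation used a between-subjects SD of [value] and a correlation of [value], giving an SD of change of [value].* If the inputs do not give an SD of change near 10.5, withdraw 0.91.

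2. **Tie the power to one primary test.** Name the treatment difference in CAPS past-week change at week 6 from the mixed model, with one degree of freedom, adjusted for baseline CAPS and for site. Site is already the blocking factor in the randomization. This replaces the rule under Site effects that tests for site differences and then switches to stratified analyses, a rule that leaves the primary analysis dependent on the data.

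Baseline adjustment can only help in this setting. The residual SD becomes SD·√(1 − ρ²) in place of SD·√(2(1 − ρ)). With an assumed between-subjects SD of 15 and ρ = 0.5, that is 13.0 against 15.0, and power with 50 per arm rises from 0.64 to 0.76. With SD 20 it rises from 0.41 to 0.52.

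The cost is a change of text. The sample size stays at 154 and no new data are needed. The stated power may become less favourable. If the authors' inputs do give 10.5, one sentence settles the first item.
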